**1. Background**

According to statistics provided by the World Health Organization, Uganda currently has the 20^th^ highest rate of maternal mortality, and the 15^th^ highest rate of infant mortality in the world.^1^ Amongst nations in Africa, Uganda has one of the highest population growth rates, with an annual increase in 3.2% and a fertility rate of 6.7%.^1^ With approximately 1.5 million pregnancies/year, it is estimated that nearly 6000 women will die due to pregnancy related complications (16 mothers/day) – numbers which are exacerbated by poverty, malnutrition, illness, and lack of access to antenatal, peri-natal and postnatal health care services.

While maternal and child mortality is prevalent nationwide, the situation is particularly problematic in remote rural regions such as Kabale, which is located in southwestern Uganda. In contrast to the urban regions of Uganda where it is reported that close to 95% of women attend at least one antenatal care clinic (ANC)^2^ prior to delivery , current data points to only 66% presenting for ANC in rural Kabale^3^. Additionally, compared to nearly 60% of women delivering in health centers in urban areas, only 30% of births in Kabale take place in health centers, with most births occurring at home.^3,4^

Extreme poverty and malnutrition amongst women in the region have led to high rates of anemia – studies indicate that 64% of pregnant or new mothers are suffering from anemia in Kabale – in addition to high rates of HIV and malaria. As a result, 70% of the population who deliver at home in the Kabale region, are attended only by unqualified midwives who lack the necessary training and equipment to respond to high-risk delivery complications, are facing the risk of experiencing severe bleeding (caused by post-partum hemorrhage), infection (mostly after delivery), hypertensive disorders (eclampsia), obstructed labor, and ultimately, death.^4^

There are multiple contributing factors that are preventing pregnant women living in the Kabale region from receiving maternal healthcare services from trained professionals. These include cost, access, infrastructure, and cultural attitudes.

One of the greatest barriers to maternal health is geography and distance from regional centers where maternal health services are provided. The population in Kabale is situated in smaller, rural communities scattered across a geographically mountainous region. As the majority of rural communities are lacking healthcare centers and trained professionals, pregnant women can only receive trained maternal healthcare services outside their communities. However, the distance from their local communities to the regional center where the government hospital and Kigezi Healthcare Foundation’s (KIHEFO) medical and maternity center are currently operating is immense. As a result, the majority of subsistence agriculture households cannot afford the cost to travel to regional centers for antenatal, natal and postnatal care.

Cultural attitudes surrounding childbirth, mainly the fear and stigma of receiving maternal healthcare outside home communities, is also problematic to providing pregnant women with professional medical healthcare services, and overall, reducing maternal mortality. This cultural fear is generated largely by a lack of education amongst rural populations in understanding the additional risks associated with childbirth due to realities of poverty, malnutrition, disease and illness. As a result, many pregnant women who are living in rural communities maintain the preference to give birth at home, despite lacking access to trained birth attendants who can respond to high-risk complications that arise, and facing high rates of maternal mortality.

Consultations with local health care workers and community leaders during a medical mission in March 2013 suggested that a significant additional barrier to care is that local women do not appreciate the benefits of routine antepartum screening and treatment. In fact, when antenatal medical services are offered free of charge in a local context women often fail to turn out for the program. At present, local antenatal care includes a general examination including blood pressure testing, maternal hemoglobin testing, maternal voluntary HIV counseling and testing, serology for syphilis, Hepatitis B surface antigen testing, syndromic management for sexually transmitted infections and provision of free maternal iron and folate as well as presumptive treatment for malaria using fansidar as per WHO guidelines. If HIV is diagnosed, free antiretrovirals are offered as part of the national program. Similarly, benzathine penicillin G therapy is administered to patients with a positive treponemal test for syphilis with the resultant prevention of long-term maternal complications as well as the severe complications to the infant of congenital syphilis. Hepatitis B vaccine is also offered to all infants of mothers who are Hep BsAg positive (as per routine Ugandan national guidelines).

Although this comprehensive approach would offer many potential benefits to both mother and infant, local thought leaders believe that women do not see these interventions as significant, and therefore do not present for care even when mobile free clinics are brought into their communities. The impression of the local medical staff is that the importance of these “low tech” interventions are not appreciated in the general community. On the other hand these same thought leaders have suggested that women would present for care to have the concrete outcome of “seeing a picture of the baby”. In addition to being appealing to women who are pregnant for personal reasons, studies have shown that obstetric ultrasound imaging can prevent many serious complications of pregnancy (listed previously) by providing early diagnosis and intervention. For example, by providing useful information such as whether or not the mother is carrying twins, has an ectopic pregnancy or placenta previa, a mother and her partner can make an informed decision about whether or not to deliver at home with untrained professionals, or a health center where they can receive life-saving treatment.^1^ Furthermore, the World Health Organization (2003) recognizes ultrasound technology as ideally suited to low and middle income countries, as it is relatively low-cost, low input, and easily maintained and transported. Additionally, studies conducted on the use of ultrasound technology in two rural hospitals in Rwanda have indicated that after an initial training period, an ultrasound program led by local health care providers can be sustainable and lead to accurate diagnoses.^2^ Ultrasound imaging is beneficial to rural populations as it is a simple a non-invasive procedure. This helps to reduce levels of fear from women who have previously maintained their cultural preferences for receiving treatment and giving birth with untrained birth attendants in their local villages.^3^

We carried out a small pilot program in March 2013 that screened 48 antenatal women with free mobile ultrasound. We found the technology to work well within the local context and women routinely expressed their appreciation and impression that they were glad they had come and would recommend it to their peers. All of the above routine antenatal screening and interventions were offered at the same time as per routine local guidelines.

**2. Hypothesis / Objectives of the study**

Hypothesis:

Although antenatal care in rural Uganda is hindered by geographic constraints, lack of personal finances and government health care infrastructure, cultural attitudes towards western medicine are also an important concern. Many women do not present for antenatal care as they feel that “just blood testing and tablets” are not reason enough to present for antenatal care. Offering free obstetric ultrasound will significantly increase the number of women in rural Uganda who present for antenatal care.

Objectives:

A) To improve maternal attendance at antenatal clinics and thus achieve the following outcomes by implementing routine National Ugandan screening recommendations:

i) To reduce Mother to Child Transmission of HIV

ii) Reduce Mother to child transmission of syphilis, Hepatitis B and prevent malarial complications during pregnancy

iii) Improve maternal preference for delivery with medical professionals

B) Identify antepartum risks for increased perinatal complications by offering free ultrasound. In particular, multiple birth, breech presentation, or low-lying placenta; with arrangements to be made for delivery in specialized facilities for women who are thus found to be in need.

**3. Design and Methodology**

Communities in the Kabale District will be assessed for population size, demographics and birth rate. Communities that have similar characteristics will be selected and contacted to engage in the study. Communities who agree to participate in this study will be contacted and community leaders will make announcements at local schools, churches, and community events regarding the upcoming free antenatal clinics. During these announcements the community will be told either a) that there will be structured maternal health camps [sMHC] offering free obstetric ultrasound [fOBU] or b) that there will be sMHCs with no mention of the fOBU. In actuality, to assure that all women are given the benefit of optimal care, all SMHCs will provide fOBU, but only the advertising messages will differ between groups. Communities will be stratified by catchment population (small, medium or large) prior to randomization and assignment to the intervention or control group. The sMHCs will be organized in collaboration with TO – the WORLD and KIHEFO. The four-pronged approach of MTCT elimination will be followed in the design of the sMHC. This will include primary prevention of HIV, prevention of unintended pregnancies, prevention of vertical transmission and assuring linkages to care treatment and follow-up. Each sMHC will take place over a 12-hour period. All women who appear for clinic will be registered, with demographics recorded, and go through a triage process. They will then receive pre-test counseling for HIV, followed by blood sample collection for onsite testing for HIV/syphilis/hepatitis B, they will then go through family planning sessions, receive a fOBU, will be seen by a triage nurse and then be seen by an MD or DDS (Dentist) depending on their triage needs. All routine care including iron, folate and intermittent presumptive therapy for malaria will be offered free of charge. Women who are found on ultrasound screening to have potential obstetrical high risk pregnancies (low lying placenta, twins, potential birth defects) will be referred for local obstetrical services in Kabale (the regional referral center). Ultrasound will be performed using two Sonosite 180 portable ultrasonographic units operated by two technicians trained to levels of competency as dictated by national guidelines.

**4. Justification for Use of Deception**

Patients will not initially be informed of the study design, which seeks information on how availability of ultrasound will impact their decision to seek out antenatal care. They will receive a questionnaire that will seek to clarify their rationale for seeking care. As this is a major study outcome which could be impacted by knowing the study design, it will be necessary to withhold this information until after the study questionnaire has been completed, i.e. if patients are told that we are aiming to clarify whether the availability of obstetrical ultrasound leads to greater turnout, they may conclude that this is an outcome that the researchers hope to see, and thus to “help the researchers” they will report that ultrasound availability motivated their decision to present for care. Therefore, only after the patients complete their study questionnaires, will they then be informed of the study goals. We do not believe that the study would be possible without this initial (and temporary) non-disclosure, and further there is no potential negative adverse impact of the non-disclosure on the patients. It is important to note that screening obstetrical ultrasound has not previously been available in these communities. The addition of this service (which is routine in developed countries) is an enhancement in service. Therefore, not advertising the availability of the ultrasound in the half of those communities that are randomized to receiving the service but not the notification of it’s availability does not pose a reduction in care from that offered routinely in rural Uganda

**5. Inclusion/Exclusion Criteria**

Inclusion:

The participants must all be residents of the Kabale Region. All pregnant women aged 18 and above who present to one of the sMHCs will be included.

Exclusion:

Pregnant women under the age of consent (under 18 years); and any males or non-pregnant females who attend the health camps will be excluded from the study.*

Notes:

*All participants excluded from the study will still be offered free medical and dental care as part of a mobile free medical/dental clinic that will be offered in the same community at the same time but in a neighbouring location. For pregnant women under the age of 18, fOBU will also be offered.

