**A.8 QUALITY ASSURANCE**

A.8.1 What procedures are in place to ensure the quality of the data?

*Guidance notes:*

*For qualitative data (for example) what procedures will be used to check translations or compare data obtained from different sources?*

*For quantitative data (for example) how will transcription errors be minimised?*

*Give some detail on how methods are going to be piloted, if appropriate*

The primary objective of our study is to assess the number of women who present to ANCs at the different facilities with or without the intervention. There will be ample staff available at triage to capture all of the patients who present to each clinic thus ensuring that the maximal data will be captured at each sMHC.

The same two research associates will deliver the maternal survey to every patient enrolled into the study with the help of the same two translators. This will ensure consistency in the questions being asked and the answers that are translated. The vast majority of the answers will be very simple “yes or no” and thus will be subject to very little inter-interviewer discrepancy.

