**7. Statistical Design**

The study design is a cluster randomized controlled trial, whereby communities will be randomly assigned to two groups: the intervention communities will receive outreach messaging that includes information about the availability of fOBU included in medical/dental clinics and the control communities will receive outreach messaging about the availability of medical/dental clinics without mention of the availability of fOBU (although fOBU will be available in both study arms). Outcomes will be assessed at the patient-level (clustered) and the facility-level (ANC uptake).

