**8. Recruitment Process**

As described above, participants will be recruited from communities in the Kabale Region by announcements that will be made by community leaders at local schools, churches, and community events regarding the upcoming free antenatal clinics. During these announcements the community will be told either a) that there will be structured maternal health camps (sMHC) offering free obstetric ultrasound (fOBU) or b) that there will be sMHCs with no mention of the fOBU. The recruitment materials will all be in the local language, and will be translated by the local health care workers who are fluent in English and the local Luchiga dialect.

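### Communities are randomised but uptake is compared by camp attended, so a control-community woman who goes to an advertised-ultrasound camp would count as intervention uptake and be lost from control

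*Protocol*

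**What the plan says.** - **Unit of randomisation.** Section 7 states that "communities will be randomly assigned to two groups". Under section 3, "all SMHCs will provide fOBU, but only the advertising messages will differ between groups".
- **Who is eligible.** Section 5 sets the residence condition for the whole region: "The participants must all be residents of the Kabale Region". It continues: "All pregnant women aged 18 and above who present to one of the sMHCs will be included". Section A.5.3 has the same region-wide rule, without the age limit.
- **What is counted.** Section A.8.1 gives the primary objective as to "assess the number of women who present to ANCs at the different facilities with or without the intervention", with enough triage staff to "capture all of the patients who present to each clinic". Section 7 calls ANC uptake the facility-level outcome. Section A.7.1 compares uptake between arms by linear regression at health-centre level.
- **How the message travels.** Section 8 describes "announcements that will be made by community leaders at local schools, churches, and community events".
- **What is recorded.** Sections A.4 and 3 have demographics taken at registration. Neither names village of residence or gives it a use.

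The protocol does not restrict a camp to its own community, assign a woman to the arm of her home community, or set a distance between study communities.

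**The concern.** Randomisation follows where women live, while the count follows where they attend. The two agree only if nobody crosses.

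The trial's premise is that the promise of an ultrasound brings women in. A control-community woman is not told that her own camp offers one. If she hears that a neighbouring camp does, she has a reason to go there, and public announcements are hard to confine to one village.

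A woman who switches camps moves both counts in the direction of the hypothesis, although she would have attended anyway. A control-community woman who would otherwise have stayed at home also raises the intervention count. What is at stake is whether the primary comparison measures more women attending or the same women attending elsewhere.

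**Working it through.** **Inputs**

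- Planned uptake, section A.5.4: 0.70 against 0.52, a difference of 0.70 − 0.52 = 0.18.
- Crossing rate: not in the documents. Assumed range: 2% to 10% of control-community attenders.
- Equal numbers of eligible women per arm: assumed.

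The protocol has no figure for crossing to reproduce. Its stated 144 women per group does not follow from 0.70 against 0.52 (pooled formula 115; with continuity correction 125). That is a separate matter, and nothing below uses it.

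**1. Switching, no true effect.** Let p = 0.52 be uptake in both arms and c the share of control-community attenders who go to an intervention camp instead of their own. Counted by camp:

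- intervention = p(1 + c)
- control = p(1 − c)
- spurious difference = 2cp

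| c | Intervention | Control | Spurious difference |
|---|---|---|---|
| 2% | 0.530 | 0.510 | 2.1 points |
| 5% | 0.546 | 0.494 | 5.2 points |
| 10% | 0.572 | 0.468 | 10.4 points |

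**2. Switching when the planned difference is seen.** Suppose 0.70 against 0.52 is observed by camp. By residence, control is 0.52/(1 − c) and intervention is 0.70 − c × 0.52/(1 − c).

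| c | Intervention by residence | Control by residence | Difference |
|---|---|---|---|
| 2% | 0.689 | 0.531 | 15.9 points |
| 5% | 0.673 | 0.547 | 12.5 points |
| 10% | 0.642 | 0.578 | 6.4 points |

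**3. New attenders.** Suppose instead that 5% of all control-community pregnant women, who would otherwise have stayed away, attend an intervention camp, and there is no other effect.

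- By camp: 0.52 + 0.05 = 0.57 against 0.52, or +5 points.
- By residence: 0.52 against 0.52 + 0.05 = 0.57, or −5 points.

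**4. Both together.** As shares of all control-community pregnant women, let d be those diverted from their own camp and e the new attenders. Let δ be the effect of the message on attendance by intervention-community women. Then:

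- difference by camp = δ + 2d + e
- difference by residence = δ − e

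Counting by residence removes the displacement term 2d. It does not remove e, whose sign it reverses. With these two mechanisms alone, δ lies between the two counts.

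**The case against.** **Eligibility is not attribution.** Section 5 says who may enter, not which arm her data belong to. Section A.8.1 is about data quality, and a SAP that is not shown might assign cross-attenders. This is fair as far as it goes. But A.7.1, A.8.1 and section 7 all point to a count by facility, and no SAP can reassign women whose village was never recorded. Applying the residence criterion means asking where a woman lives, but only to the level of the region.

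**Crossing may be rare.** Section A.2 and the Background describe villages isolated by mountains and households unable to pay for travel to regional centres. The Background adds that women often stay away even from free clinics in their own communities. This stands as a reason why the bias may be small. It does not rule out crossing between neighbouring study villages, since the distances described are to the regional centre.

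**Direction is not certain overall.** Control women who hear of the ultrasound and attend their own camp pull the difference towards zero. Women from non-study villages could attend camps in either arm. Both points stand. Nothing ensures that these effects cancel the displacement.

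**Stronger readings a reader might infer.** None of these is supported:

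- *The primary result is biased.* The documents show that the count permits bias, not that crossing will occur.
- *Five per cent crossing costs 10 points.* That is true only of 5% of all control-community women who all switch camps, giving 0.57 against 0.47. At uptake 0.52 this is 0.05/0.52 = 9.6% of attenders.
- *A catchment denominator is broken.* Catchment population is used only to stratify; no uptake denominator is defined.
- *Residence attribution removes all distortion.* Steps 3 and 4 show that it does not.

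**Conclusion.** The concern holds as a risk of unknown size. As written, the plan can count displaced control-community women as intervention uptake, and this mechanism favours the hypothesis.

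Under no true effect, uptake of 0.52 and equal arms, switching by 2%, 5% or 10% of control-community attenders gives about 2, 5 or 10 spurious points, against a planned 18. The crossing rates are assumptions. The 18 points are also only a yardstick, because note 1 to A.5.4 ties the uptake rate to at least one ANC visit in pilot work rather than to attendance at a camp. No false-positive rate is offered here, since a calculation on individual women would ignore the clustering that A.7.1 says will be adjusted for.

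The remedy corrects displacement at almost no cost, provided that its own weakness is stated and both counts are shown.

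**What to change.** 1. Add village of residence to the demographics already taken at registration.
2. Define primary uptake for each study community as its residents presenting at any study camp, analysed by that community's randomised arm.
3. Report women from outside all study communities separately. Their care is unchanged.
4. Report the number of cross-attenders in each direction, and give the count by camp attended as a sensitivity analysis.
5. State the limitation: control women newly drawn by the ultrasound message count in control, which dilutes the apparent effect and can reverse it (0.52 against 0.57 in step 3). This is why both counts are needed.

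The cost is one field on an existing form and a few sentences of analysis text. Some attendees leave the primary count, and the residence count is exposed to the dilution in item 5.

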**6. Age Range**

Based on a pilot study conducted in 2013 it has been determined that the average age range of participants will be between 18-40 years of age. Any patient presenting to clinic who is under 18 years of age will be excluded from the research study but still offered all medical and dental services.

